## Abstract

**Background:**

Studies centered on the detection of cognitive impairment and its relationship to cardiovascular risk factors in elderly people have gained special relevance in recent years. Knowledge of the cardiovascular risk factors that may be associated to cognitive impairment could be very useful for introducing treatments in early stages - thereby possibly contributing to improve patient quality of life.

The present study explores cognitive performance in people over 65 years of age in Salamanca (Spain), with special emphasis on the identification of early symptoms of cognitive impairment, with the purpose of detecting mild cognitive impairment and of studying the relationships between this clinical situation and cardiovascular risk factors.

**Methods/Design:**

A longitudinal study is contemplated. The reference population will consist of 420 people over 65 years of age enrolled through randomized sampling stratified by healthcare area, and who previously participated in another study. Measurement: a) Sociodemographic variables; b) Cardiovascular risk factors; c) Comorbidity; d) Functional level for daily life activities; and e) Study of higher cognitive functions based on a neuropsychological battery especially adapted to the evaluation of elderly people.

**Discussion:**

We hope that this study will afford objective information on the representative prevalence of cognitive impairment in the population over 65 years of age in Salamanca. We also hope to obtain data on the relationship between cognitive impairment and cardiovascular risk factors in this specific population group. Based on the results obtained, we also will be able to establish the usefulness of some of the screening tests applied during the study, such as the Mini-Mental State Examination and the 7 Minute Screen test.

**Trial registration:**

ClinicalTrials.gov: NCT01327196

## Background

The study of cognitive impairment in elderly people presently constitutes an important challenge, considering that the population life expectancy has increased significantly in the last decades. With advancing age, and particularly after 60 years of age, the prevalence of cognitive impairment increases almost exponentially, and represents one of the main causes of disability among the elderly[1-5]. In the European Union it has been estimated that over 5 million inhabitants suffered dementia in the year 2005 (1.14-1.27% of the population), with a total of 583,208 registered cases in Spain that year [6]. In the region of Castilla y León, the estimated prevalence of dementia is 6.4% in people aged 65 years and older - representing about 43,500 individuals. This situation now constitutes an important clinical, healthcare and socioeconomic problem, in view of the sanitary and care requirements involved, the important family impact, and the scarcity of effective therapeutic resources. Few studies on the economical cost of dementia have been conducted in our setting, though the estimated cost exceeds 9000 euros per patient and year, considering only the direct healthcare costs: drugs, diagnostic studies, medical visits, etc. If the indirect costs associated with the disease are also taken into account, then the figure per patient reaches 19,000 euros per year. During the year 2004, the cost totaled over 8200 million euros in Spain alone [7].

Although cognitive impairment is the most relevant symptom, dementia is usually also associated to different behavioral, psychological and functional manifestations that affect the functional and executive capacities of the individual - interfering with normal family, social and occupational activities, and lessening the quality of life of both the patients and their caregivers. Dementia is one of the main causes of early patient institutionalization. It has been estimated that behavioral or neuropsychiatric symptoms can manifest in 50% of all elderly patients with dementia, and the frequency is moreover higher among institutionalized individuals [4,8]. These symptoms can show diverse presentations, in any evolutive stage of the disease, and typically manifest in multiple and oscillating forms [4].

At present, the most common cause of dementia is Alzheimer's disease (AD), of probable multifactorial origin (genetic, environmental, toxic, etc.), followed by vascular dementia (VD). The role of cerebrovascular disease as a cause of dementia has been recognized for over a century. We are now witnessing a redefinition of the different forms of VD, with introduction of the concept of vascular cognitive impairment, designed to identify the early stages of a process hypothetically amenable to preventive intervention and treatment. Together with the classical vascular lesions (arterial and lacunar infarctions), other types of cerebrovascular lesions are becoming known such as leukoaraiosis or incomplete infarctions, which contribute to the development of intellectual impairment, and increased insight is being gained to the clinical, neuropsychological and radiological correlations involved. Behavioral and psychological manifestations are increasingly investigated and recognized as symptoms inherent to VD [9,10]. Descriptive, analytical and interventional epidemiological studies have underscored the relevance of vascular factors as causal agents in dementia [11,12]. Another important epidemiological aspect in the field of vascular cognitive impairment refers to cognitive impairment presenting in stroke patients. Up to 30% of all patients with cerebral infarction develop dementia in the three months following stroke - this representing a 9-fold greater risk versus the controls without stroke [12]. The repetition of stroke may trigger dementia in some but not in all cases, and many patients develop dementia without any apparent underlying clinical event. Furthermore, in many cases the observed dementia corresponds to Alzheimer's disease instead of vascular dementia. This point is important if the vascular component of mixed dementia is amenable to preventive treatment.

Different strategies have been proposed for the prevention of dementia, though none have yielded positive results. Given the absence of quality clinical evidence supporting their use, drug treatments (statins, hormone replacement therapy or nonsteroidal antiinflammatory drugs (NSAIDs)) are not advised for the primary prevention of dementia [11]. This discouraging reality is applicable to most dementias, since these are due to Alzheimer's disease, but it is possible to prevent the second most common cause of dementia, i.e., vascular dementia [1,3,4], which manifests as a consequence of cerebrovascular disease. Regarding the primary prevention of dementia, the PAPPS study [13] recommends remaining socially and mentally active, physical activity, and the observation of healthy living habits, with adequate control of cardiovascular risk factors - particularly correct blood pressure control.

Cardiovascular diseases are the main cause of death in Spain, and are attributable particularly to cerebrovascular disorders and ischemic heart disease.

Arterial hypertension is a systemic condition that preferentially affects three body organs: the heart, kidneys and brain. In contrast to the heart and kidneys, which are systematically evaluated in clinical practice, brain function is often neglected. Hypertension and dementia are common disorders in the population over 65 years of age. It has been estimated that 8% and 65% of these individuals suffer dementia and hypertension, respectively [14]. From this age onwards, the prevalence of dementia increases exponentially, doubling every 5 years and reaching 28.5% in people aged 90 years or older (EURODEM study)[15,16].

The results of epidemiological studies in reference to the association between these two disorders vary depending on the methodology employed [17]. Thus, while cross-sectional studies have reported contradictory results [18-21], longitudinal surveys point to a positive relationship between the presence of arterial hypertension in middle age and mild cognitive impairment 15-20 years later [22-24]. No such association has been observed when arterial hypertension develops at an older age [25-27]. Skoog et al. [28] found arterial hypertension at 70 years of age to be greater in subjects who developed dementia between 79 and 85 years of age. However, during the years preceding the onset of dementia, blood pressure decreases in comparison with those subjects who do not develop dementia. Similar findings have been published by Hanon [29] and Verghese [30]. The correlation between blood pressure and mild cognitive impairment is more complex than a simple lineal relationship. Chronic hypertension predisposes to mild cognitive impairment and the development of dementia, but a drop in blood pressure can be observed in the phase prior to the development of diffuse cognitive impairment [28].

Likewise, no clear effect of antihypertensive treatment has been observed in terms of the prevention of mild cognitive impairment in hypertensive patients. A Cochrane review [31] concludes that "*There was no convincing evidence in the reviewed trials to suggest that lowered blood pressure prevents the development of dementia or cognitive impairment in hypertensive patients without manifest prior cerebrovascular disease". *However, on considering the evidence of the cross-sectional, longitudinal and observational studies together with the evidence generated by the randomized clinical trials (RCTs), moderately solid support is found of the notion that hypertension in adult life - particularly when not treated effectively - exerts a negative effect upon cognition, and contributes to the development of dementia and Alzheimer's disease in old age [17,19,32]. There is less evidence from these studies that the same negative effect upon cognition is present with hypertension at an older stage in life [19].

The relationship between cholesterol and mild cognitive impairment is contradictory. There are several cross-sectional PAPPS studies with differing results [33,34]. There are also several longitudinal studies reporting a positive association between total cholesterol and mild cognitive impairment, while three observe no association, and one reports a negative association [35].

In reference to diabetes mellitus, a number of studies have reported an association with the prevalence of dementia, though others have found no such relationship. Biessesls et al. [36], following an analysis of several longitudinal studies, found the incidence of dementia to increase between 50-100% in subjects with diabetes versus individuals without diabetes. Associations have also been described with blood glucose [37] and glycosylated hemoglobin. In this sense, for every 1% rise in HbA1c, an increased risk of cognitive impairment or dementia has been reported (OR 1.40: CI 1.08-1.83)[38].

Metabolic syndrome groups a series of cardiovascular risk factors; as a result, an increased risk of target organ damage could be expected in patients with this syndrome. However, few studies have evaluated the association between metabolic syndrome and the development of dementia or mild cognitive impairment. Some cross-sectional [39] and longitudinal studies [40] have described an association between metabolic syndrome and cognitive impairment. Thus, while a certain relationship appears to exist, the risk of dementia in individuals with metabolic syndrome has not been firmly established, and it is not clear whether such risk is greater than the sum of its components [38].

Comorbidity among people over age 65 is common and conditions the prognosis of other concomitant disease processes, with an acceleration of the possible complications. Different methods are available for assessing comorbidity. Charlson proposed a numerical scale using a list of pathological conditions: the Charlson comorbidity index [41,42]. This index was designed to classify comorbidities for prognostic purposes, and posteriorly has been used as a control of the influence which comorbidity may exert in different situations. The Charlson index has not been used in the analysis of cardiovascular risk factors and cognitive impairment. Likewise, no study has been made of the association of cardiovascular risk as estimated from the risk scales and cognitive impairment in individuals over 65 years of age.

Less than one-half of all patients with Alzheimer's disease have been diagnosed, and of these subjects, approximately 25% are receiving some kind of treatment [43]. The number of individuals with undiagnosed cognitive impairment is therefore expected to be high, particularly in groups with certain risk factors. One of the factors explaining why many people with cognitive impairment have not been diagnosed is related to the fact that we have no cognitive impairment screening tool in the elderly population sufficiently warranted by the scientific community and the professionals who care for such patients.

Based on a neuropsychological battery especially adapted for the study of elderly people, we will carry out a study of cognitive performance in people over 65 years of age in Salamanca (Spain), with special emphasis on the identification of early symptoms of cognitive impairment, with the purpose of detecting mild cognitive impairment and of studying the relationships between this clinical situation and cardiovascular risk factors.

The following objectives have been established:

1. To study the cognitive performance of people over 65 years of age in Salamanca, with a view to estimating the prevalence of the different manifestations of cognitive impairment and its severity.

2. To analyze the association of cardiovascular risk factors (diabetes, arterial hypertension, dyslipidemia and metabolic syndrome) in patients over age 65 with mild cognitive impairment.

3. To use the Mini - Mental State Examination (MMSE) and the 7 Minute Screen test as screening tools for cognitive impairment in the elderly population under study.

## Methods/Design

### Design and study population

A longitudinal study will be carried out, since we will be starting from a reference population of 327 people over 65 years of age living in the city of Salamanca (Spain) and who participated in the cross-sectional study entitled "Sociosanitary needs of people over 65 years of age in the city of Salamanca", financed by the regional health authorities (SOCIO673/01/08). Randomized sampling is contemplated, stratifying for healthcare area.

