## Discussion

There are studies in which a link has been established between cardiovascular risk factors and the development of dementia. However, few studies have related mild cognitive impairment to cardiovascular risk. We hope that this study will afford objective information on the representative prevalence of mild cognitive impairment in the population over 65 years of age in Salamanca.

We will conduct an analysis of the cardiovascular risk factors in the selected sample, allowing us to establish the possible correlation between certain cardiovascular risk markers and mild cognitive impairment. If found, such a correlation would be very useful for future studies designed to allow a certain prevention of such impairment, based on control of the cardiovascular risk factors.

The results obtained moreover will allow us to assess the predictive capacity in detecting cognitive impairment from the applied screening tests (MMSE and 7 Minute Screen), since their results will be contrasted with those of the detailed neuropsychological explorations. The importance of the early detection of cognitive impairment should be stressed, since it will allow the start of adequate treatment and thus can contribute to improve patient quality of life.

Lastly, we wish to point out that since a randomized population-based sample from the city of Salamanca is involved, the information obtained may be of increased representativeness - particularly considering that many studies suffer bias due to the lack of purely randomized criteria in selecting the participants.

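### Prevalence is claimed for everyone over 65 in Salamanca, but the closed earlier cohort holds nobody who has passed 65 since the first survey, and the net bias is of unknown sign

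*Protocol article*

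**What the plan says.** The Design and study population section states "we will be starting from a reference population of 327 people over 65 years of age living in the city of Salamanca" and identifies them as participants in an earlier cross-sectional survey. The Abstract gives another number but the same origin: "The reference population will consist of 420 people over 65 years of age enrolled through randomized sampling stratified by healthcare area", again people who took part in a previous study. The Power analysis section places the sampling from the health-card database in the first study. The only other sampling sentence is "Randomized sampling is contemplated, stratifying for healthcare area".

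Objective 1 is to study people over 65 in Salamanca "with a view to estimating the prevalence of the different manifestations of cognitive impairment and its severity". The Discussion expects "objective information on the representative prevalence of mild cognitive impairment in the population over 65 years of age in Salamanca" and argues that "since a randomized population-based sample from the city of Salamanca is involved, the information obtained may be of increased representativeness". On the age gradient, the Background says that "the prevalence of dementia increases exponentially, doubling every 5 years and reaching 28.5% in people aged 90 years or older".

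The Statistical analysis section plans a comparison with the baseline evaluation and a breakdown of results by age and sex. Methodological limitations names death and worsening physical or mental impairment as the main causes of loss. The interval between the two studies is not stated.

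**The concern.** The random draw represented people over 65 at the time of the first survey. When the same people are examined again after an interval of k years, the youngest is 65 + k. Residents who reached 65 in the meantime belong to the population named in the claim but cannot be in the sample. This would happen even if every earlier participant attended, so it is separate from non-response. The Methodological limitations section does not mention it.

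Two results are affected. The crude prevalence answers for an older age range than the one named. A population-level comparison of the two evaluations would also mix the ageing of the cohort with real change.

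**Working it through.** **1. The plan's own figure.** Inputs from Power analysis: p = 0.16 (mild impairment plus dementia), error d = 0.04, alpha 0.05, population 34,020.

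- n0 = 1.96² × 0.16 × 0.84 / 0.04² = 322.7
- n = 322.7 / (1 + 321.7/34,020) = 319.7, so 320, as stated.
- Half-width with 327 people: 1.96 × √(0.16 × 0.84/327) = 3.97 points. With 420 people: 3.51 points.

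**2. Can the source cover the target?** Source: earlier participants, all over 65 at that time. Target: everyone over 65 now. Ages from 65 to 65 + k are in the target and not in the source. The ambiguous sampling sentence does not change this, because a random draw from earlier participants cannot contain people who were too young for the earlier survey.

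**3. Size of the age effect alone (illustration).** The documents give neither the interval, nor the age distribution, nor an age gradient for mild impairment. Assumptions:

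- Stationary population aged 65 to 99; annual mortality 1.0% to 1.5% at 65, multiplied by exp(0.10) per year of age. S(a) is survival from 65 to age a.
- Overall prevalence 16%.
- Gradient A: the whole 16% doubles every 5, 7.5 or 10 years of age, capped at 90%.
- Gradient B: only dementia doubles every 5 years. It is set at 7%, between the 6.4% and 8% in the Background. Mild impairment is flat at 16% − 7% = 9%.

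Missing share = 1 − ΣS(a ≥ 65 + k)/ΣS(a ≥ 65). Shift = S-weighted mean prevalence at a ≥ 65 + k, minus 16%.

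| Interval k | Missing share of over-65s | Shift, A | Shift, B |
|---|---|---|---|
| 1 year | 4.8–5.6% | +0.5 to +0.8 points | +0.3 to +0.4 |
| 2 years | 9.5–11.1% | +1.0 to +1.7 | +0.7 to +0.8 |
| 4 years | 18.8–21.9% | +2.2 to +3.7 | +1.4 to +1.7 |
| 5 years | 23.4–27.1% | +2.8 to +4.9 | +1.9 to +2.2 |

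With the mortality slope varied from 0.09 to 0.11, the upper end for A at 2 years becomes +1.8.

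Two years is itself an assumption. The earlier project's code ends in 01/08 and ethics approval is dated August 2010. Reading the code as a date is a guess.

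**4. The opposing effect.** Let R be the retention of impaired people relative to unimpaired people. The age effect is cancelled when R = (0.16/0.84) / (p′/(1 − p′)), where p′ is the shifted prevalence.

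- At 2 years with p′ = 17.5%: R = 0.1905/0.2121 = 0.90.
- Over the table's range at 2 years: R about 0.89 to 0.93 under A, and about 0.95 under B.
- With R = 0.7 and p′ = 17.5%, observed prevalence = 0.175 × 0.7 / (0.175 × 0.7 + 0.825) = 0.1225/0.9475 = 12.9%, which is below 16%.

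A modest difference in attendance is therefore enough to cancel or reverse the age effect.

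**The case against.** **Direction.** A reader might infer that the reported prevalence will be too high. The documents do not support that. Methodological limitations expects losses mainly from death and worsening impairment. The first study used home interviews (Power analysis), whereas the present one requires attendance at a university faculty (Procedure). These features act downward, and step 4 shows how little is needed to offset the age effect. One qualification applies: death also removes people from the city's population, so the downward bias proper comes from living earlier participants who do not attend. This objection stands and limits the conclusion to an unknown net sign.

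**Size.** At 2 years the age effect is well inside the planned 4 points. Under gradient A it passes 4 points only at about 5 years with a steep gradient, and nothing in the documents points to so long an interval. The doubling is stated for dementia, so carrying it over to mild impairment is an assumption, although the Background also says that cognitive impairment in general rises almost exponentially after 60. This also stands, with one reservation: the shift is systematic, so a larger sample would not reduce it.

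**Silence on standardisation.** The article condenses a fuller plan, so the absence of a standardisation step is not held against it. The point is that the stated target exceeds what the stated source can cover. A breakdown by age cannot restore a band with no participants.

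**Longitudinal purpose.** Change as the same people age is what a longitudinal study sets out to measure. That is correct for within-person change, but not for a comparison of population prevalence. The objectives on risk-factor associations and screening tests do not depend on a representative youngest band.

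**Hedging.** The Discussion says only that the information may be more representative. Objective 1 and the expected representative prevalence still name the whole population over 65.

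**Conclusion.** The concern holds in a limited form. The sample is a closed cohort that was already over 65 at an earlier survey, and it cannot represent the current population over 65, because the youngest ages are absent by design. The age effect alone is upward: about 0.7 to 1.8 points at an assumed 2-year interval, resting on an assumed age distribution, mortality and gradient, and below the planned 4-point error. Impairment-related loss and on-site testing act downward, so the net bias has no known sign. Opposing errors could yield a plausible figure that is still not representative. The disagreement between 327 and 420 is a separate matter and does not affect this conclusion.

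**What to change.** - State the interval between the two evaluations.
- Restrict the prevalence claim in Objective 1, the Abstract and the Discussion to the attained ages, 65 plus the interval and over.
- Within those ages, report prevalence by age band and standardise it directly by age and sex to the current health-card population, the database already used for the first study's sampling.
- Compare population prevalence between the two evaluations only at matched ages. Keep within-person change as a separate longitudinal analysis.

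The cost is one population table and a weighted estimate, with a slightly wider confidence interval and a narrower stated age range. Standardisation has two limits that the text should state: it cannot fill the empty youngest band, and it does not by itself correct for impairment-related loss.
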